### Power and sample size calculations

Our primary analysis will determine whether the study intervention is associated with increased knowledge of LDKT, one week after the transplant evaluation. Because the randomization of patients is clustered by evaluation date, sample size and power calculations for testing the effect of the intervention must be based on the number of evaluation days randomized to each condition, the number of patients per evaluation day, the expected intra-class correlation (ICC) among patients within a cluster (ICC indicates within-group similarity on the outcome), and the estimated difference between conditions in, and variability of, transplant knowledge scores. Based on previous research [40], we estimate that patients in the intervention arm will have 10-20% higher transplant knowledge at 1 week post-baseline than patients in the standard-of-care arm. Assuming a conservative ICC of 0.4, we calculated that with 250 patients in each of the two study arms from approximately 100 evaluation days per study arm (2–3 patients per evaluation day), a two-sample t-test with type 1 error of 0.05 would have at least 95% power to detect a 10-20% difference in knowledge scores. In summary, to have sufficient power to detect differences in the primary and secondary outcomes, this study should include 250 patients in each education condition at 1 week post-evaluation.

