**Methods/design:**

We report the protocol of the Enhancing Living Donor Kidney Transplant Education (ELITE) Study, a cluster randomized trial of an educational intervention to be implemented during initial transplant evaluation at a large, suburban U.S. transplant center. Five hundred potential transplant candidates are cluster randomized (by date of visit) to receive either: (1) standard-of-care (“usual”) transplant education, or (2) intensive education that is based upon the *Explore Transplant* series of educational materials. Intensive transplant education includes viewing an educational video about LDKT, receiving print education, and meeting with a transplant educator. The primary outcome consists of knowledge of the benefits, risks, and process of LDKT, assessed one week after the transplant evaluation. As a secondary outcome, knowledge and understanding of LDKT are assessed 3 months after the evaluation. Additional secondary outcomes, assessed one week and 3 months after the evaluation, include readiness, self-efficacy, and decisional balance regarding transplant and LDKT, with differences assessed by race. Although the unit of randomization is the date of the transplant evaluation visit, the unit of analysis will be the individual potential transplant candidate.

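### Enrolment of 500 equals the number required with 1-week data, leaving nothing for loss, and the claim of sufficient power for secondary outcomes rests on no calculation

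*Protocol article*

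**What the plan says.** The only power calculation in the article is in Power and sample size calculations. It concerns LDKT knowledge one week after the evaluation. "Assuming a conservative ICC of 0.4", and "with 250 patients in each of the two study arms from approximately 100 evaluation days per study arm" (2 to 3 patients per day), it states that "a two-sample t-test with type 1 error of 0.05 would have at least 95% power to detect a 10-20% difference in knowledge scores". The section closes with the requirement that "this study should include 250 patients in each education condition at 1 week post-evaluation". The purpose it gives for that number is "to have sufficient power to detect differences in the primary and secondary outcomes".

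The abstract gives the total: "Five hundred potential transplant candidates are cluster randomized (by date of visit").

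Four other parts of the article bear on this:

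- **Measurement timepoints:** the outcomes are collected by telephone at 1 week and 3 months.
- **Statistical analysis:** the main analysis is per-protocol. Multiple imputation of missing data for all enrolled participants is a sensitivity analysis.
- **Other secondary outcomes and Secondary analyses:** readiness is dichotomised. Self-efficacy and decisional balance are continuous. Changes from 1 week to 3 months are also analysed.
- **Secondary analyses, last paragraph:** race, earlier actions to learn about transplant and health literacy are tested for interaction with the intervention on knowledge.

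**The concern.** Two stated numbers fit together only if there is no loss. The requirement is 250 per arm with 1-week data, and the number randomised is 250 per arm. Yet the primary outcome depends on a later telephone call, the main analysis set can exclude participants, and the article itself plans for missing data. Any loss leaves the trial short of its own stated requirement.

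The closing sentence also carries a conclusion about one outcome over to all secondary outcomes. No effect size, SD, event rate or ICC is given for any of them, and the change outcomes need a second call. If the sentence stands, a null secondary result could be reported as coming from a trial planned with enough power to find a difference, when the plan has not shown that.

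**Working it through.** **Inputs from the article:** 250 patients and about 100 evaluation days per arm, so m = 250/100 = 2.5 patients per day; ICC 0.4; alpha 0.05; power of at least 95%.

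**Assumptions, because the article does not state them:** a two-sided test, the loss rates, the readiness proportions, and the same ICC for secondary outcomes. The normal approximation is used throughout.

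**1. The plan's own figure**

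- Design effect = 1 + (m − 1) × ICC = 1 + 1.5 × 0.4 = 1.6.
- Effective n per arm = 250/1.6 = 156.25.
- Difference detectable with 95% power = (1.960 + 1.645) × √(2/156.25) = 0.408 SD. For 80% power it is (1.960 + 0.842) × √(2/156.25) = 0.317 SD.

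The article gives no SD and does not say whether 10-20% is relative or in points, so its 95% cannot be reproduced in score points. It can be read only as 95% at 0.41 SD.

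**2. Enrolment against requirement**

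To hold 250 per arm at 1 week, enrolment would have to be 250/(1 − loss):

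- 10% loss: 250/0.90 = 278 per arm, 556 in total.
- 20% loss: 250/0.80 = 313 per arm, 626 in total.

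With 500 enrolled, those losses leave 225 or 200 per arm.

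**3. Effect of the shortfall on primary power**

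Power = Φ(0.408/√(2/n_eff) − 1.96), starting from exactly 95%.

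| Loss | Analysed per arm | n_eff, 100 days per arm kept | Power | n_eff, design effect held at 1.6 | Power |
|---|---|---|---|---|---|
| 0% | 250 | 250/1.6 = 156.3 | 95.0% | 156.3 | 95.0% |
| 10% | 225 | 225/1.5 = 150.0 | 94.2% | 225/1.6 = 140.6 | 92.8% |
| 20% | 200 | 200/1.4 = 142.9 | 93.2% | 200/1.6 = 125.0 | 89.7% |

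In the first pair of columns the design effect falls because fewer patients remain per day (m = 2.25, then 2.0).

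With 200 analysed per arm and 100 days kept, the difference detectable with 95% power is 3.605 × √(2/142.9) = 0.427 SD.

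**4. Secondary outcomes at the full 250 per arm, n_eff = 156.25**

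- Continuous, 0.2 SD: Φ(0.2/0.1131 − 1.96) = Φ(−0.19) = 42%.
- Continuous, 0.3 SD: Φ(0.3/0.1131 − 1.96) = Φ(0.69) = 76%.
- Continuous, 0.4 SD: Φ(0.4/0.1131 − 1.96) = Φ(1.58) = 94%.
- Readiness, 40% versus 50%: SE = √((0.24 + 0.25)/156.25) = 0.056; Φ(0.10/0.056 − 1.96) = Φ(−0.17) = 43%.
- Readiness, 40% versus 55%: about 76%.
- Readiness from an assumed control proportion of 30% to 50%: 80% power needs a difference of about 15 to 16 percentage points, and 95% power about 20.

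These figures assume no loss. The 3-month change outcomes need both calls and will have fewer patients.

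**The case against.** **Primary power may be untouched.** The article says at least 95%, not exactly 95%. If 10% means 2 of the 20 points, power is 97.7% or more for an SD of 3 to 4, even with 20% loss and an assumed coefficient of variation of 0.5 in day size. The ICC is called conservative: at 0.408 SD with 200 per arm over 100 days, power is 96.1% at ICC 0.2 and 97.3% at ICC 0.1. This stands. It rules out calling the primary comparison underpowered, but it does not reconcile 250 per arm with data and 250 per arm randomised.

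**The article is condensed.** A loss allowance, the SD and the scale of the 10-20% may sit in the full protocol. This stands for the SD and the scale, which are not counted here as errors. It does not answer the mismatch, because both of those numbers are printed in the article.

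**A reader might infer that the design lacks power for its secondary outcomes.** The article does not support that. Without secondary effect sizes, SDs or rates it cannot be shown, and a difference of 0.4 SD would have about 94% power. The claim is unsupported rather than shown to be false.

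**A reader might also infer that the power sentence covers the race, literacy and prior-education interactions.** It does not say so. Those are tests on knowledge, and no power is explicitly claimed for them. Figures for a race interaction would also need an assumed share of Black participants.

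**Unequal day sizes.** The article mentions up to six candidates in a day, but that counts attendees, not enrolled participants. Any coefficient of variation is therefore an outside assumption, and the finding does not rest on one.

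**Conclusion.** The concern holds in two limited parts.

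First, the number enrolled equals the number required with 1-week data, so any loss or per-protocol exclusion puts the trial below its own stated size. The cost to primary power is small: about 1 to 5 percentage points at an assumed 10% to 20% loss, and only if power starts at exactly 95%.

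Second, the statement that 250 per arm suffices for the secondary outcomes has no calculation behind it. At the plan's own sizes and ICC it would hold for differences near 0.4 SD, but not for 0.2 SD or for a 10-point difference in readiness.

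The secondary figures assume that the knowledge ICC applies to those outcomes. At ICC 0.1, for example, readiness of 40% versus 50% has about 55% power instead of 43%. Neither part affects the validity of the primary test.

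**What to change.** Leave enrolment at 500 and reword the power section:

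1. State an assumed loss at 1 week and give the power for the number then analysed. For example, at 20% loss, 200 analysed per arm over 100 days per arm with ICC 0.4 gives 95% power for 0.43 SD. While the text is open, add the target difference in score points and its SD.
2. Remove the secondary outcomes from the closing power sentence, or replace the claim with detectable differences for readiness and for the 3-month change outcomes under a stated 3-month loss.
3. Label the interaction tests exploratory.

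The cost is rewording, with stated figures slightly less favourable than those now printed. Nothing changes in recruitment, conduct or the primary analysis.

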## Discussion

We designed the ELITE study to determine whether an educational intervention, implemented on the day of the transplant evaluation at the transplant center, increases knowledge of LDKT among potential transplant candidates, assessed one week and 3 months after the evaluation. Additional secondary outcomes include readiness, self-efficacy, and decisional balance regarding transplantation and LDKT, assessed one week and 3 months after the evaluation. We also will compare the effectiveness of the different educational interventions for Black and non-Black patients and patients of varying levels of health literacy.

This study is notable for testing an intervention that is physically delivered at the transplant center, in a method consistent with standard clinical care. If effective, more intensive transplant education could be replicated and easily incorporated into transplant evaluations in the approximately 235 transplant centers nationwide. Surprisingly, few interventions have targeted CKD patients being evaluated at the transplant center [42,56]. Instead, most prior interventions have targeted CKD patients in nephrologists’ offices [57,58], dialysis units [59,60], and patients’ homes [56,61]. By bringing together CKD patients who have some preexisting interest in transplant, the transplant evaluation, offers an opportunity to efficiently and effectively educate these patients about LDKT.

Our study design has several potential limitations. Our educational intervention is a relatively brief, one-time event that occurs solely at the transplant evaluation. Typically, the study participants in the intensive education arm will spend less than one hour watching videos and meeting with the Transplant Educator. An intervention that includes additional education sessions (e.g. after the transplant evaluation) may be more effective, albeit less practical. In addition, all study participants in the intervention arm receive the same intervention. If we were able to measure study participants’ knowledge and interest in LDKT prior to the transplant evaluation, then we could tailor the intervention for each participant’s level of readiness.

In conclusion, the results of the ELITE study have the potential to guide clinical care and patient education in kidney transplant centers. Studies of behavioral and educational interventions implemented during the transplant evaluation at the transplant center will enable the transplant community to determine the best ways to educate the CKD population regarding transplant.

## Abbreviations

LDKT: Live donor kidney transplant; DDKT: Deceased donor kidney transplant; ESRD: End-stage renal disease; CKD: Chronic kidney disease; NVS: Newest vitals sign; SBMC: Saint Barnabas Medical Center; ELITE study: Enhancing living donor kidney transplant education study.
